### Screening and randomisation

Patients with clinical features of infection will be screened for sepsis using standard clinical procedures including recording of vital signs, and collection of blood samples including full blood count, urea and electrolytes and a venous blood gas analysis including serum lactate. Those who have a systolic blood pressure < 100 mmHg on arrival, or who develop this during their ED stay, will receive a 1000-ml IV fluid challenge with isotonic crystalloid over a maximum of 60 min. Patients whose blood pressure remains < 100 mmHg, or whose blood pressure falls below this threshold within 60 min of completing the fluid challenge, and who do not have any exclusion criteria will be invited to participate in the trial. Participants who fulfil the eligibility criteria and for whom consent is obtained (see ‘Ethics and consent’ below) will be randomised (1:1) to one of the study arms. The treating clinician will perform randomisation in real time using a dedicated, secure, password-protected web-based interface. Allocation concealment will be maintained until the conclusion of the online randomisation process. Randomisation, using a computer-generated random sequence, will be stratified by site in pre-allocated blocks of 2 and 4, thus making it impossible to predict the last allocation in a block. For practical and safety purposes randomised trial participants and the treating team will not be blind to the trial intervention. The staff conducting the laboratory analyses and the trial statistician will be blinded to the treatment allocation. The screening and enrolment procedure is summarised in (see Additional file 2: Figure S1).

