Randomisation	Eligible participants in whom a consent process has been commenced will be randomised to either the fluid-volume restricted or the fluid-liberal (standard-care arm)
Randomisation procedure	• Eligibility assessment and randomisation conducted by clinical staff with support by research personnel (in person or by telephone)
	• Computer-generated randomisation sequence
	• Real-time web-based randomisation
	• 1:1 randomisation in blocks of 2 or 4
Blinding	• Un-blinded to patients and to treating team
	• Blinding of laboratory staff and data analysts
Data collection methods	• Paper CRF completed for each participant
	• CRF populated by research staff in real time or from clinical record
	• Subsequent data entry into secure database by trained research assistant
	• Audit of data entry against source documentation
Data collected	• All fluids administered pre-randomisation
	• All fluids administered post randomisation – 6 h (recorded hourly)
	• All fluids administered over 6–24 h
	• Urine output to 24 h
	• Vital signs at enrolment and hourly until 6 h
	• Antimicrobials – agent, dose and time administered
	• Corticosteroid administration
	• Source of sepsis (suspected/proven)
	• Charlson Comorbidity Score
	• Microbiological/serological results from samples obtained in first 24 h
	• Sequential Organ Failure Assessment (SOFA) score at admission and at 24 h
	• Acute Physiology and Chronic Health Evaluation (APACHE) II score (peak first 24 h)
	• Acute Kidney INjury (AKIN) score up to 7 days
	• Study blood sampling at enrolment (T0), 3 h (T3), 6 h (T6) and 12–24 h (T24)
Statistical analysis	• Intention-to-treat analysis
	• Statistician blinded to treatment allocation
Data and safety monitoring	• DSMC – emergency physician, intensive care physician, statistician
	• SAE reporting to study coordination centre within 24 h
	• DSMC review all SAE
	• Periodic data review by DSMC and recommendations to PI in event of study conduct of SAE issues
	• Trial coordinator will monitor trial conduct at each site at regular intervals
Ethics and governance	• HREC approvals obtained for all sites
	• Clinical governance (site-specific authority) procedures in place for all sites
	• Any subsequent protocol amendments to be submitted to lead ethics site with appropriate dissemination to participating study sites
	• The study will be conducted in accordance with GCP
Consent	• Where possible, prospective informed consent will be obtained

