### Limitations

An open-label design confers challenges but is unavoidable given the nature of the trial intervention. Potential bias arises due to the treating clinician being aware of the treatment allocation. The pragmatic nature of the trial allows for some latitude for the clinician to determine fluid volumes within set parameters; however, it is difficult to control for individual behaviours and treating physician preference for one approach over another. An additional potential challenge may be the reluctance to give fluid in the standard-care arm on the basis of perceived potential harms (the rationale for the trial). To counter this, regular feedback and educational sessions with clinicians will occur throughout the trial. For this pilot trial, the primary feasibility outcomes are objective measures (e.g. fluid volumes, processes of care). Clinical outcome measures are also objective and pre-specified, e.g. mortality, organ failure. However to minimise any potential risk of bias, a physician-investigator will adjudicate clinical outcomes blinded to group allocation. Similarly, laboratory analyses will be conducted in blinded fashion.

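### Site-stratified blocks of 2 and 4 do not make the last allocation in a block impossible to predict, and the protocol should not say so

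*Protocol article*

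**What the plan says.** Under Screening and randomisation, the protocol article states that the computer-generated sequence is stratified by site "in pre-allocated blocks of 2 and 4, thus making it impossible to predict the last allocation in a block". Table 1 (under Aim, design and setting) repeats the scheme as "1:1 randomisation in blocks of 2 or 4". The relative frequency of the two sizes is not given.

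The same section says "The treating clinician will perform randomisation in real time using a dedicated, secure, password-protected web-based interface", and that "randomised trial participants and the treating team will not be blind to the trial intervention". The web system conceals each allocation until randomisation is complete. Table 1 gives the eligibility assessment to clinical staff, supported by research personnel in person or by telephone.

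Several exclusion criteria rest on judgement: whether a non-sepsis cause contributes to the hypotension, whether there is a clinical need for fluid replacement, and whether fluid loading or vasopressor support would be appropriate. The primary outcome counts fluid given before randomisation. The Limitations section lists "treating physician preference for one approach over another" as hard to control but does not mention predictability of the next allocation.

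**The concern.** Mixing block sizes is usually meant to stop an observer knowing where a block ends. With sizes of only 2 and 4, within a site and with open treatment, that protection is thin. Each completed block is balanced, so the running difference between arms at a site equals the difference within the current block. Web concealment hides the list, but it does not prevent inference from allocations already known.

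If a clinician could anticipate the next arm, two things might follow. Judgement-based exclusions could be applied differently according to the expected arm. Fluid given before randomisation, which is part of the primary outcome, could also be altered in anticipation: patients qualify after 1000 ml and are excluded only above 2000 ml. Blinding the laboratory staff, the statistician and the outcome adjudicator protects measurement and analysis, not the choice of whom to enrol.

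**Working it through.** **Inputs from the protocol article.** 1:1 allocation, blocks of 2 and 4, stratified by site (Screening and randomisation; Table 1); 8 sites and 100 participants (Table 1); 42 enrolled at submission (Trial status). The protocol attaches no figure to predictability, so there is none to reproduce. The sample size of 43 per group does not enter this point.

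**Assumptions.** The two sizes are equally likely, with a range of one third to two thirds of blocks being size 2. The guesser knows every earlier allocation at the site. Sites recruit equally, so 100/8 = 12.5, or about 12 per site. The strategy is to name the arm that is behind, or toss a coin when the arms are level.

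**Block of 2 (AB or BA).** The first place is a coin toss (0.5) and the second is always right (1). Sum 1.5 of 2 = 75%.

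**Block of 4 (three patterns, and their mirror images).**
- AABB: 0.5 + 0 + 1 + 1 = 2.5
- ABAB: 0.5 + 1 + 0.5 + 1 = 3
- ABBA: 0.5 + 1 + 0.5 + 1 = 3
- Mean 8.5/3 = 2.833 of 4 = 70.8%

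In every pattern the final place scores 1: it is always filled at a difference of one and always restores balance.

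**Mixture, equal shares.** Correct guesses: (1.5 + 2.833)/(2 + 4) = 72.2%. With one third size-2 blocks: (0.5 + 1.889)/3.333 = 71.7%. With two thirds: (1 + 0.944)/2.667 = 72.9%. At 12 patients per site, simulation gives 71.6% for equal shares.

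**Where the guesses succeed (equal shares, mean block length 3).**
- Level tally: (1 + 5/3)/2 = 1.333 places per block.
- Difference of one: (1 + 2)/2 = 1.5 places, of which (1 + 5/3)/2 = 1.333 go to the arm behind, or 88.9%.
- Difference of two: 1/2 × 1/3 = 0.167 places, always certain.
- Unequal tally overall: 1.667/3 = 55.6% of allocations, guessed right (1.333 + 0.167)/1.667 = 90% of the time.
- Immediately after the first patient of a block, the next is the opposite arm with probability 1/2 + 1/2 × 2/3 = 83%.

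**Certain allocations.** A lead of two can arise only when a block of 4 opens with two in the same arm. Its third and fourth places are then both known.
- Share of all allocations: 1/2 × 1/3 × 2/3 = 11.1% in the long run (8.3% to 13.3% over the range; about 10% at 12 per site).
- Share of blocks whose last allocation is certain: 1/2 × 1/3 = 1/6 = 17% (11% to 22%).

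**Alternatives, by the same measure.** Equally likely blocks of 4, 6 and 8 give 68.1%. A big-stick rule tosses a coin unless the site difference has reached 3, and then forces the arm behind. Over 12 patients, the chance of being at the limit before allocations 4, 6, 8, 10 and 12 is 0.250, 0.3125, 0.328, 0.332 and 0.333, and zero before the others. The forced share is 1.556/12 = 13.0%, and correct guesses are 0.5 + 0.130/2 = 56.5%.

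**The case against.** The strongest reply is that 72% describes an ideal observer. The treating team knows its own patient's arm, but nothing in the protocol says clinicians see their site's allocation history. Recruitment was also sparse: 42 participants at six sites from July 2016 to 22 June 2017. If all six sites were open throughout, that is about 50 weeks × 6/42, or one patient per site every 7 weeks. A rotating emergency roster would seldom hold the full ordered tally during a resuscitation. This stands, and it makes the percentages upper bounds. It does not remove the route: research personnel support randomisation, some sites have research nurses who screen, and site investigators complete the case report forms.

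A reader might infer that the protocol calls all prediction impossible. It does not; the sentence covers only the last place in a block, although that is where the claim fails most plainly. A reader might also take the Limitations remark on clinician preference as an admission of selective enrolment. It concerns latitude over fluid volumes after allocation.

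The protocol has checks that could reveal selection: pre-randomisation volume is reported separately, the proportions eligible and enrolled are feasibility outcomes, baseline data are analysed, and the biomarker models adjust for centre, severity and comorbidity. These help with detection and partly with adjustment. They do not prevent selection.

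**Conclusion.** The statement about the last allocation is wrong for the design it describes. The last place of every block follows the arm that is behind, and it is deducible with certainty in about 1 block in 6 (11% to 22%). Overall guessability is at most about 72%, with about 11% of allocations certain in the long run. These figures rest on equal shares of the two block sizes, or the stated range, and on a guesser with complete knowledge of the site's allocations. The size-2 blocks raise guessability slightly above fixed blocks of 4 (72.2% against 70.8%).

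The documents do not support the stronger conclusion that enrolment, fluid volume, mortality or biomarkers have been biased. Guessability is not bias, and no input allows the size of any shift to be estimated. Publication of the block sizes likewise does not show that site staff knew them while enrolling. In an open-label feasibility pilot whose primary contrast is driven largely by arm-specific fluid instructions, this should be fixed, but it is not a fatal flaw.

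**What to change.** Delete the claim of impossibility and add predictability of allocation within sites to the Limitations section.

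For allocations not yet issued (100 − 42 = 58 at submission), keep site as the stratum, drop blocks of 2, and load a less predictable scheme whose parameters are withheld from site staff. There are two options:
- Larger, randomly varied blocks. The gain is modest: about 68% correct guesses with sizes 4, 6 and 8.
- A big-stick or biased-coin rule. The gain is larger: about 56% for a big stick with limit 3 at 12 per site. Its downsides should be stated: site imbalance can reach 3 instead of 2, and about 13% of allocations are forced, against about 10% certain at present for someone tracking the full order. Starting the rule from each site's current tally keeps the limit intact across the change.

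The cost is regenerating the unissued lists in the existing web system, a dated note of the change, and one edited sentence. If enrolment has closed, the limitation should still be reported, alongside pre-randomisation volume by arm and the proportion of eligible patients enrolled by site. The scheme should not be carried into the larger trial that this pilot is meant to inform.

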### Study interventions

#### General management – all participants

Supplemental oxygen to maintain SpO_2_ > 92%Antibiotics within 60 min of enrolmentVentilation (non-invasive) or intubation and mechanical ventilation, if clinically indicated, using a lung preventive strategy as recommended by SSC guidelines [4]; consider ketamine for induction to minimise risk of hypotensionAll fluids administered (bolus or maintenance) subsequent to enrolment to be balanced isotonic crystalloid during the first 6 h. Hypotonic fluids and synthetic colloids and 0.9% saline are to be avoided. Blood products and albumin may be given at treating clinician discretion. Actual (unadjusted) volumes of all non-crystalloid fluids will be recordedFluid management will be as per study protocol for the first 6 h post randomisation regardless of whether the patient remains in the ED or is transferred to ICU or to a ward. For patients with an unanticipated transfer to theatre for surgery during this time the trial protocol will be suspended

#### Restricted-volume (±early vasopressor) arm (see Additional file ***3***: Figure S2)

Management following randomisation after the initial 1000-ml fluid bolus for the next 6 h:Continue fluid infusion intravenously at a *maintenance rate* of 1–2 ml/kg/h (max 150 ml/h) via infusion pump, as clinically indicatedIf SBP < 90 mmHg or mean arterial pressure (MAP) < 65 mmHg:Start noradrenaline* infusion by peripheral IV route (large vein) and titrate to maintain MAP at 65–70 mmHgInsertion of urinary catheter and hourly urine output measuresInsertion of central venous access (central venous catheter (CVC)/ peripheral intravenous central catheter (PICC)) and commencement of central noradrenaline infusion once correct position confirmed by chest X-ray. Alternatively, at physician discretion and according to local protocol, if the anticipated duration of vasopressor requirement is less than 6 h the infusion can continue via a dedicated secure peripheral large venous cannula if the patient is monitored in a critical care environment and there is no other indication for central accessArterial line at the discretion of the treating clinicianTitration and weaning of vasopressors as per treating clinician and local protocolsAdditional therapies, e.g. vasopressin, corticosteroids at the treating clinician’s discretionIf, in the judgement of the treating clinician (based upon clinical assessment, central venous pressure (CVP), ultrasound, etc.), the patient remains hypovolaemic, a further 1000-ml isotonic crystalloid bolus is permitted
Reassess each hour for the first 6 h. At each reassessment consider need for further fluid bolus based upon clinical assessment, including:Mental status, skin perfusionUrine outputRepeat lactate (if initially elevated)Ultrasound/echocardiography or CVP if available

If the treating clinician judges additional fluid to be required, administer an additional *250-ml* isotonic crystalloid IV bolus.

#### Standard treatment arm (see Additional file ***4***: Figure S3)

Management following randomisation after the initial 1000-ml fluid bolus for the next 6 h:Give a *second fluid bolus* of 1000 ml (balanced isotonic crystalloid)ReassessIf SBP ≥ 90 mmHg and MAP ≥ 65 mmHg give maintenance rate of 1–2 ml/kg/h (max 150 ml/h) via infusion pump, as clinically indicatedIf SBP < 90 mmHg or MAP < 65 mmHg:i.Give further *500-ml* boluses, at least every 30 min, until the treating clinician judges euvolaemia to be achievedii.Once euvolaemia is deemed present (e.g. inferior vena cava (IVC) non-collapsing on ultrasound, CVP > 8 mmHg, distended neck veins, etc.) and if the patient remains hypotensive:Start noradrenaline* infusion by peripheral IV route (large vein) and titrate to maintain MAP at 65–70 mmHgInsertion of urinary catheter and hourly urine output measuresInsertion of a central venous access (CVC/PICC) and commencement of central noradrenaline infusion once correct position confirmed by chest X-ray. Alternatively, at physician discretion and according to local protocol, if the anticipated duration of vasopressor requirement is less than 6 h the infusion can continue via a dedicated secure peripheral large venous cannula if the patient is monitored in a critical care environment and there is no other indication for central accessArterial line at the discretion of the treating clinicianTitration and weaning of vasopressors as per treating clinician and local protocolsAdditional therapies, e.g. vasopressin, corticosteroids at the treating clinician’s discretion

Reassess each hour for the first 6 h. At each reassessment consider the need for further fluid boluses based upon clinical assessment, including:Mental status, skin perfusionUrine outputRepeat lactate (if initially elevated)Ultrasound/echocardiography or CVP if available

If the treating clinician judges additional fluid to be required, administer an additional *500-ml* isotonic crystalloid IV bolus.

*An infusion of metaraminol via a peripheral IV cannula may be considered as an alternative to noradrenaline in accordance with local hospital policy.

#### Study measurements

##### Clinical

All fluids administered pre-randomisationAll fluids administered post-randomisation – 6 h (recorded hourly)All fluids administered over 6–24 hUrine output to 24 hVital signs at enrolment and hourly until 6 hAntimicrobials – agent, dose and time administeredCorticosteroid administrationSource of sepsis (suspected/proven)Charlson Comorbidity Score [28]Microbiological/serological results from samples obtained in first 24 hSequential Organ Failure Assessment (SOFA) score [29] at admission and at 24 hAcute Physiology and Chronic Health Evaluation (APACHE) II score [30] (peak first 24 h)

##### Laboratory

Study blood sampling:Enrolment (T0), 3 h (T3), 6 h (T6) and 12–24 h (T24)Plasma and serum samples (total 5 ml) at each sampling time pointBlood gas (arterial or venous) including lactate and haemoglobin at each sampling time pointBlood samples should not to be taken during fluid-bolus administration and should be taken from the opposite arm from any maintenance fluid being administered

Samples will be centrifuged and the extracted sera/plasma divided into 500-μl aliquots and stored at −80 °C for subsequent batch analysis.

### Strategies to ensure protocol compliance and data integrity

Digital copies of de-identified Case Report Forms will be submitted electronically to the trial coordination centre at the following time points; enrolment, completion of hospital stay, 28 days and 90 days. This will allow for checking and data queries to be undertaken in a timely manner. This will also identify any protocol deviations and provide opportunity for feedback to the site investigator. A trained research assistant at the trial coordination centre will upload data into a secure trial database. There will be periodic internal audits of data accuracy and compliance.

### Outcome measures

Consistent with the exploratory pilot nature of this study, multiple feasibility, process-of-care, clinical and mechanistic outcomes will be evaluated. The primary outcome relates to achieving a difference in the volume of intravenously administered fluid to the groups. All analyses will be by intention-to-treat.

#### Primary outcome

A clinically and statistically significant difference in mean total fluid volume administered at 6 h post randomisation (including pre-randomisation). In addition pre- and post-randomisation volumes will be reported separately. See ‘Statistical methods and sample size calculation’ below.

#### Secondary outcomes: feasibility

Proportion of screened patients eligibleProportion of eligible patients enrolledEnrolment rate (i.e. number of enrolments per month per site)Protocol compliance

#### Secondary outcomes: process-of-care

Admission rate to ICU versus general wardRates and timing of CVC insertionPeripheral versus central administration of vasopressors

#### Secondary outcomes: clinical

Mortality (all-cause) at 90 days post enrolmentICU length of stayHospital length of stay (acute)Hospital-free days to day 90 (acute)Organ failure

o Cardiovascular▪ Administration of vasopressors▪ Duration of vasopressor requirement (h)▪ Vasopressor-free days to day 28

o Respiratory▪ Requirement for ventilation (non-invasive ventilation (NIV)/intermittent positive-pressure ventilation (IPPV))▪ Duration of ventilator support (h)▪ Ventilator-free days to day 28

o Renal▪ Requirement for renal replacement therapy (RRT)▪ Duration of RRT▪ RRT-free days to day 28▪ Acute Kidney Injury Network (AKIN) score to day 7 [31]

#### Laboratory/mechanistic outcomes

Peak values, as well as patterns of expression over time (T0–T24), will be analysed for a range of biomarkers and compared between the groups including:Atrial natriuretic peptideTroponinInflammatory cytokines
o Interleukin (IL)-6, IL-10, resistin
Neutrophil gelatinase-associated lipocalin (NGAL; a biomarker of renal injury)Endothelial cell activation biomarkers
o sVCAM, sICAM, sE-Selectin, sFlt-1
Soluble markers of glycocalyx degradation
o Heparan sulphate, syndecan-1, hyaluronan

All laboratory analyses will be performed and the results collated by laboratory staff blinded to the study group allocation. As a pragmatic, open-label trial, treating clinicians and participants will be aware of the treatment allocation.

The schedule of enrolment, interventions and assessments is shown in Fig. 1.

**Fig. 1 Fig1:**
[figure not shown]
Standard Protocol Items: Recommendations for Interventional Trials (SPIRIT) Figure

### Statistical methods and sample size calculation

The primary outcome is the achievement of a minimum clinically significant relative difference of 33% in the total cumulative fluid volume administered until T6 (including pre-randomisation fluids). In the control arm of an Australasian, multicentre randomised controlled trial of early goal-directed therapy in septic shock, the mean total volume administered within the first 6 h was 4200 ± 2650 ml [32]. We aim to achieve a reduction of 33%, to a mean of 2800 ± 1800 ml over 6 h in the restricted-volume arm compared to the standard-care arm. This will require 43 participants in each group to achieve 80% power with *α* = 0.05. This pilot trial is not designed to have sufficient power to detect differences in secondary clinical outcomes.

The trial will also measure a range of biochemical markers. There is limited relevant data to inform sample size calculations for these analyses. Based upon feasible recruitment within a 12-month time period, a sample size of 100 is attainable. This will allow a margin of safety for achieving differences in the primary outcome. It will also enable the detection of differences between means of the two treatment groups of 55.6% of the standard deviation (or larger) for the measured biomarker, with 80% power and *α* = 0.05. This calculation is based upon a cross-sectional *t* test, not a repeated measures test (which affords additional power). As such, these calculations are conservative.

Baseline clinical and demographic data will be analysed using chi-square or Fisher’s exact test for categorical data, and the Wilcoxon rank-sum test for continuous data.

Where biomarkers are normally or log-normally distributed, linear mixed models with maximum likelihood estimation will be employed to analyse the pattern over time. Differences in the pattern of expression of each biomarker between the groups will be tested by the interaction of time and group in the model. Additional covariates will be added to adjust for treating centre, illness severity and comorbidities. For biomarkers with skewed distributions resistant to successful transformation, quantile regression with per-person cluster adjustment will be used.

A biostatistician will perform the statistical analysis.

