	3. Transfer from another hospital
	4. More than 2000 ml intravenously administered fluid has been given (pre-hospital, in ED, or both)
	5. Likely requirement for immediate surgery
	6. Age < 18 years
	7. Pregnancy (confirmed or suspected)
	8. Patient in extremis or death deemed imminent and inevitable
	9. Patient wishes or comorbidities such that either fluid loading or vasopressor support is not considered clinically appropriate
Intervention	*Intervention arm*:
	Commence vasopressor infusion (± maintenance IV fluid) if SBP < 90 mmHg or mean arterial pressure (MAP) < 65 mmHg). Reassess hourly next 6 h and administer further 250-ml IV fluid bolus if required
	*Comparator arm*:
	Give a second 1000-ml fluid bolus plus further 500-ml boluses as clinically indicated until judged to be euvolaemic. Commence vasopressor infusion (± maintenance IV fluid) if SBP < 90 mmHg or MAP < 65 mmHg). Reassess hourly next 6 h and administer further 500-ml IV fluid bolus if required
Primary outcome measure	Total volume of intravenously administered fluid (including pre-randomisation) at 6 h
Secondary outcome measures	• Mortality (all-cause) at 90 days post enrolment
	• ICU length of stay
	• Hospital length of stay
	• Hospital-free days to day 90
	• Organ failure
	o Cardiovascular
	▪ Requirement for vasopressors
	▪ Duration of vasopressor requirement (h)
	▪ Vasopressor-free days to day 28
	o Respiratory
	▪ Requirement for ventilation (NIV/IPPV)
	▪ Duration of ventilator support (h)
	▪ Ventilator-free days to day 28
	o Renal
	▪ Requirement for renal replacement therapy (RRT)
	▪ Duration of RRT
	▪ RRT-free days to day 28
	▪ AKIN score to day 7
Laboratory/mechanistic outcome measures	Peak values, as well as patterns of expression over time (T0–T24), will be analysed for a range of biomarkers and compared between the groups including:
	• Atrial natriuretic peptide
	• Troponin
	• Inflammatory cytokines
	o IL-6, IL-10, resistin
	• NGAL (a biomarker of renal injury)
	• Endothelial cell activation biomarkers
	o sVCAM, sICAM, sE-Selectin, sFlt-1
	• Soluble markers of glycocalyx degradation
	o Heparan sulphate, syndecan-1, hyaluronan
Feasibility outcome measures	• Proportion of eligible patients enrolled
	• Randomisation errors
	• Compliance – protocol violations
	• Proportion with completely recorded data
	• Proportion with complete study blood sampling
Sample size	50 per arm/100 total

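### The biomarker power calculation is called conservative, but the time-by-group interaction test named for the biomarkers has more power than the quoted t test only if serial correlation is high

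*Protocol article*

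**What the plan says.** All the relevant text is in the protocol article, mostly under Statistical methods and sample size calculation.

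- With 100 participants (Table 1: "50 per arm/100 total"), the trial is said to detect "differences between means of the two treatment groups of 55.6% of the standard deviation (or larger) for the measured biomarker". Power is set at 80% and α at 0.05.
- The calculation rests on a t test at a single time. The article stresses that this is "not a repeated measures test (which affords additional power). As such, these calculations are conservative".
- Later in the same section, differences in the pattern of each biomarker between groups "will be tested by the interaction of time and group in the model". The model is a linear mixed model fitted by maximum likelihood.
- Under Laboratory/mechanistic outcomes, the pattern runs from T0 to T24, and peak values are also compared between groups.
- Under Study measurements, Laboratory, there are four sampling times: enrolment (T0), 3 h, 6 h and 12–24 h.

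No within-patient correlation is given. The section says that there are few data on which to base the biomarker calculation.

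**The concern.** The t test compares the two arms' levels at one time. The interaction test asks whether the arms differ in how the biomarker changes over time. The difference between two measurements has variance 2(1−ρ) times that of one measurement, so it is noisier whenever ρ is below 0.5. A joint test over three follow-up times also spends three degrees of freedom. Repeated measures do add power for a difference in overall level or for a baseline-adjusted comparison, but that argument does not carry over automatically to the interaction.

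Reduced inflammation and endothelial activation is part of the stated hypothesis (Table 1), and the biomarker results are meant to give mechanistic support for a larger trial. If 0.556 SD is taken as a cautious limit, a null interaction could be read as evidence against effects of that size when the test may have had clearly less than 80% power to find them.

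**Working it through.** **Inputs.** From the document: 50 per arm, 1:1 allocation, α = 0.05 (taken as two-sided), 80% power, d = 0.556 SD, and four times. Assumed: ρ (range shown), equal variances, complete samples, no arm difference at T0 (expected under randomisation), and time as a categorical factor (3 df).

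**1. The plan's own figure.**
- Normal approximation: (1.960 + 0.842) × √(2/50) = 0.560 SD.
- Noncentral t: 0.566 SD.
- Power at 0.556 SD with 50 per arm: 79.4% (normal) or 78.6% (t).
- Sample size for 0.556 SD at 80% power: 51 (normal) or 52 (t) per arm.

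The stated 55.6% therefore reproduces to within one or two patients per arm.

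**2. One change from T0 (1 df).** The SD of a change is √(2(1−ρ)). By the normal approximation, power for 0.556 SD is 65% at ρ = 0.3, 79.4% at 0.5 and 95% at 0.7. Break-even with the t test is exactly ρ = 0.5.

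**3. The four-time interaction (3 df).** The noncentrality is λ = (n/2) δ′(CΣC′)⁻¹δ, where C takes each follow-up time minus T0 and δ holds the arm differences in those changes. Under compound symmetry, with p the difference at each time as a fraction of 0.556 SD, this becomes

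λ = 25 × 0.556² × [Σp² − (Σp)²/4] / (1−ρ).

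- Sustained difference, p = (0, 1, 1, 1): the bracket is 3 − 9/4 = 0.75. At ρ = 0.3, λ = 25 × 0.3091 × 0.75/0.7 = 8.28.
- Difference building by visit, p = (0, 1/3, 2/3, 1): the bracket is 14/9 − 1 = 0.556. At ρ = 0.3, λ = 6.13.

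Power uses the noncentral chi-square on 3 df (critical value 7.81):

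| ρ | 0.2 | 0.3 | 0.4 | 0.5 | 0.6 | 0.7 | 0.8 |
|---|---|---|---|---|---|---|---|
| Sustained | 61% | 67% | 75% | 83% | 91% | 97% | >99% |
| Building to T24 | 47% | 53% | 60% | 69% | 79% | 90% | 98% |

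Break-even with the t test's 78.6% is ρ = 0.45 (sustained) or 0.59 (building). Under AR(1), where ρ is the adjacent-visit correlation, it is 0.61 and 0.86.

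**4. Detectable difference of the interaction test.** Power of 80% on 3 df needs λ = 10.90. For a sustained effect, d = √(10.90(1−ρ)/(25 × 0.75)), which is 0.68, 0.64 and 0.59 SD at ρ = 0.2, 0.3 and 0.4.

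**5. T0 as a baseline.** With a common T0 mean in both arms and a joint 3-df test of the arm differences at T3, T6 and T24 (compound symmetry):

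| ρ | 0.2 | 0.3 | 0.4 | 0.5 | 0.6 |
|---|---|---|---|---|---|
| Sustained | 96% | 95% | 95% | 96% | 98% |
| Building to T24 | 77% | 77% | 79% | 83% | 88% |

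At a single time point, this model detects about 0.566 × √(1−ρ²) SD: 0.54 at ρ = 0.3 and 0.49 at ρ = 0.5.

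**The case against.** The strongest reply is that the loss of power rests on a ρ that the document does not give. The four samples come from one patient within 24 hours, and nothing in the document points to ρ below 0.5. At ρ = 0.7 the interaction test has 97% power (sustained) or 90% (building), and the article's statement is then true. This stands. It makes the claim conditional, whereas the article states it without condition.

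The coding of time is also not stated. With a linear trend on 1 df, a difference building by visit has 83% power at ρ = 0.5, against 69% on 3 df. But a sustained difference then has 75%, against 83%. The choice moves the break-even without removing it: over the patterns tried under compound symmetry, on 1 or 3 df, it lies between 0.39 and 0.60. Leaving T0 out of the modelled times would not help, because a difference that is constant over the modelled times gives the interaction nothing to detect.

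The t-test calculation also has a proper use. A peak is one value per patient, so the cross-sectional figure fits the planned peak-value comparison.

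A reader might infer two stronger points, and the document supports neither. The first is that 55.6% is an arithmetic error. The exact values are 56.0% and 56.6%, a rounding-level gap that changes no decision. The second is that the biomarker study is underpowered. That would require knowing that ρ is low, and the document does not say so.

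**Conclusion.** The unconditional description of the biomarker calculation as conservative is not supported for the test that the article names. For 0.556 SD, the interaction test has about 61–75% power for a sustained difference and 47–60% for a building one at ρ = 0.2–0.4, against about 79% for the t test. It overtakes the t test at ρ of about 0.45 to 0.6 under compound symmetry, and later under AR(1).

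These figures assume T0 among the modelled times, a 3-df test, complete samples and the stated correlation structures. The point concerns exploratory biomarker outcomes only. The primary outcome and its sample size are unaffected.

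**What to change.** Preferred: treat T0 as a baseline, either in a mixed model with a common T0 mean in both arms or with T0 as a covariate, and test the arm difference over T3 to T24. Under compound symmetry this has more power than the interaction test at every ρ from 0.2 to 0.6. It does not beat the t test everywhere: joint power for a building effect is 77–79% at ρ = 0.2–0.4, about that of the t test. The revised text should not promise more than this.

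If the interaction test is kept, delete the word conservative and quote that test's own detectable difference over a range of ρ, for example 0.68/0.64/0.59 SD for a sustained effect at ρ = 0.2/0.3/0.4. In either case, say that the 55.6% figure applies to the peak-value comparison.

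The cost is a change of wording and, for the first option, of model. All four samples are already planned, so no further patients or samples are needed.
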